### Sample size calculation

Sample size calculation is based on waist circumference.

To calculate the sample size, we used the formula described by Rutterford, Copas [40], Table 3.

**Table 3 Tab3:** Description of sample size calculation

$$\boldsymbol{m}=\frac{{\left({\boldsymbol{Z}}_{\mathbf{1}-\boldsymbol{\alpha} /\mathbf{2}}+{\boldsymbol{Z}}_{\mathbf{1}-\boldsymbol{\beta}}\right)}^{\mathbf{2}}\ \mathbf{2}{\boldsymbol{\sigma}}^{\mathbf{2}}}{{\boldsymbol{\Delta}}^{\mathbf{2}}}\left(\mathbf{1}+\left(\boldsymbol{n}-\mathbf{1}\right)\boldsymbol{\rho} \right)$$	
where? m = sample size per study arm	= 1.96 at the type 1 error of 5% = 0.842 at 80% power
σ = the standard deviation of primary outcome in the population	• Based on Uganda STEP survey [2], the standard deviation of waist circumference for women aged 18 to 49 years = 13.73.
△ = effect size = 7.4cm.	• Effect size was calculated based on Bendall, Mayr [41] , impact of the Mediterranean diet on central obesity. • Only studies with a duration below 12 months were included in the calculation as the proposed study duration is below 12 months.
(1 + (*n* − 1)*ρ*)= design effect (DE) to compensate for cluster randomisation. ▪ n = number of individuals per cluster ▪ ρ = Intra-Cluster Correlation coefficient	• For our intervention, n = 27 • ρ = 0.001 ▪ There is no data available on the intra-Cluster Correlation coefficient of waist circumference across villages for communities within Kampala. A range of 0.001 to 0.10 is demonstrated as a cost - effective and safe choice to account for the variability.

m = (1.96 + 0.842)^2^ *2*13.73^2^/7.4^2^) * (1 + (27-1) *0.001)

m = 55 participants

To cover for dropouts, m is increased by 20%, to make 66 participants.

Hence, the project aims to include 132 women in the trial, 66 in the treatment arm and 66 in the control arm

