### Data analysis

Data will be analysed using R software. To evaluate the effects of the intervention, multilevel analysis will be used. Using this technique, regression coefficients will be adjusted for the clustering of observations within sub parishes. We will define two levels in our multi-level analysis: (1) participant and (2) sub parishes. Linear mixed effect models will be used to examine the effect of the intervention on each of the outcome values. All analyses will be performed according to the intention-to treat-principle [42]. To assess changes in metabolic health between the intervention and control groups, a linear mixed effect model will be built where “time” (end line measurement (M_2_) will be compared with base-line measurement (M_1_) and post-follow up measurement (M_3_)), treatment (and interaction of time and treatment) as well as age will be specified as fixed effects, and sub parishes and participants as random factors. For all linear mixed models, compatibility with mixed-model assumptions will be checked by inspection of residual plots and Q-Q plots. In the case of heteroscedastic residuals, data will be log transformed. Tukey or Benjamini–Hochberg procedures will be applied when performing post hoc analyses to further identify differences within treatments as well as between time points. Statistical outliers will be defined as any observation which has an absolute residual exceeding 3 times the residual standard deviation. p < 0.05 will be considered significant in all analyses.

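### The planned mixed model estimates a plain difference in change from baseline; constraining baseline means to be equal across arms would give a modest gain in precision from data already collected

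*Protocol article*

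**What the plan says.** The primary outcome is reduction in waist circumference (Outcomes). Waist is measured at baseline, at three months and after the three-month follow-up (Table 4).

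The Data analysis section sets out the model. Time has three levels, with M2 compared against M1 and M3. Besides time, "treatment (and interaction of time and treatment) as well as age will be specified as fixed effects". Sub parish and participant are random. The model contains no baseline covariate and no constraint on the baseline difference between arms.

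The sample size rests on a cross-sectional standard deviation, "the standard deviation of waist circumference for women aged 18 to 49 years = 13.73", and "effect size = 7.4cm". It uses an intra-cluster correlation (ICC) of 0.001, although the article adds: "A range of 0.001 to 0.10 is demonstrated as a cost - effective and safe choice". No correlation between baseline and follow-up waist is given.

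**The concern.** Because M1 is an outcome occasion and treatment has its own main effect, the model estimates a separate baseline mean for each arm. The intervention effect is then the M1-to-M2 change in one arm minus that in the other. Age, the only covariate, is constant within a woman, so with complete data it cancels from that contrast and cannot sharpen it.

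In a randomised trial the two baseline means are equal in expectation. An analysis that uses this is more precise than a difference in change whenever r is below 1. What is at stake is precision on the primary outcome in a trial of six sub parishes, from a measurement that every woman already provides.

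**Working it through.** **Inputs from the article (Sample size calculation, Randomization).** Error rates: "1.96 at the type 1 error of 5% = 0.842 at 80% power". SD 13.73 cm; target difference 7.4 cm; ICC 0.001, cited range 0.001 to 0.10; "For our intervention, n = 27" women per cluster; six sub parishes allocated 1:1, so three per arm. **Assumed:** r between 0.5 and 0.9, equal variances at each occasion, complete data.

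**1. The plan's own figure.** m = (1.96 + 0.842)² × 2 × 13.73² / 7.4² × (1 + 26 × 0.001) = 54.06 × 1.026 = 55.46. The article prints "m = 55 participants", and 55 × 1.2 = 66. The figure reproduces, with 55.46 rounded down.

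**2. What the interaction estimates.** With M2 as reference, the arm-by-M1 term is the arm difference at M1 minus the arm difference at M2. With its sign reversed, this is the difference in mean change. A generalised least squares check of the planned model (18 women per sub parish) gave the same standard error with and without age: 2.642, 2.047 and 1.671 cm at r = 0.5, 0.7 and 0.8.

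**3. Precision at the plan's ICC.** Relative to a comparison of follow-up values, the variance factor is 2(1 − r) for change and 1 − r² for baseline adjustment. The ratio is (1 − r²) / [2(1 − r)] = (1 + r)/2. The standard error for follow-up values alone is 13.73 × √(2/55) × √1.026 = 2.652 cm. Multiplying it by the square root of each factor gives:

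| r (assumed) | SE, change (cm) | SE, adjusted (cm) | Variance ratio | Power for 7.4 cm, change vs adjusted |
|---|---|---|---|---|
| 0.5 | 2.65 | 2.30 | 0.75 | 79.7% vs 89.7% |
| 0.7 | 2.05 | 1.89 | 0.85 | 95.0% vs 97.4% |
| 0.8 | 1.68 | 1.59 | 0.90 | 99.3% vs 99.6% |
| 0.9 | 1.19 | 1.16 | 0.95 | both above 99.9% |

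The powers are normal approximations on the article's inputs and make no allowance for having only six clusters.

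**4. Constrained baseline under clustering.** Take a sub parish effect that is constant over time, as in the planned model, and k women per sub parish (55/3 ≈ 18 evaluable; 66/3 = 22 recruited). The ratio becomes (1 + c)/2, where c is the M1–M2 correlation of sub parish means: c = [ICC + (r − ICC)/k] / [ICC + (1 − ICC)/k]. At r = 0.8 and k = 18:

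- ICC 0.001: c = 0.04539/0.05650 = 0.803, ratio 0.902.
- ICC 0.10: c = 0.13889/0.15000 = 0.926, ratio 0.963.

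Across ICC 0.001 to 0.10, r = 0.5 to 0.9 and k = 18 or 22, the constrained model was more precise in every case checked (ratios 0.75 to 0.98).

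**5. Individual-level analysis of covariance under clustering.** Let b = (r − ICC)/(1 − ICC). Its variance is proportional to ICC(1 − b)² + (1 − ICC)(1 − b²)/k, against 2(1 − r)/k for change. At ICC 0.10, r = 0.8, k = 22: b = 0.778, so 0.00494 + 0.01616 = 0.02110, against 0.01818, a ratio of 1.16. Over r = 0.5 to 0.9 and k = 18 or 22, the ranges are:

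- ICC 0.001: 0.75 to 0.95.
- ICC 0.05: 0.99 to 1.04.
- ICC 0.10: 1.06 to 1.40.

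**The case against.** The planned contrast is a standard analysis. It matches an outcome defined as a reduction, and it is unbiased over randomisation. The choice is between two accepted methods, and nothing in the section is in error. That stands: the loss is of efficiency only.

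The loss may also be small. At r = 0.8 the standard error is 1.68 against 1.59 cm. Since the sample size uses a cross-sectional SD, the planned contrast already beats its design precision whenever r exceeds 0.5. That stands too, on the article's own inputs.

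A reader might infer something stronger: that six clusters make chance imbalance likely, and that the change analysis then over-corrects it. Given an observed individual-level imbalance, the shift is (1 − r) times that imbalance, for example 0.2 × 3 = 0.6 cm at r = 0.8. But having few clusters is a reason to expect imbalance between sub parishes, and a persistent difference of that kind is what the change contrast removes. The documents therefore do not support a charge of bias, and the six-cluster argument points the other way.

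A reader might also infer that any baseline adjustment would do. Step 5 shows otherwise. With stable sub parish effects, and inside the article's own ICC range, an individual baseline covariate removes the sub parish effect only in part and can be less precise than the planned contrast.

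**Conclusion.** The point holds as a modest, nearly free gain in efficiency. The planned effect is a valid difference in mean change. A common-baseline model would reduce its variance by about 5% to 15% at the plan's ICC of 0.001 for r between 0.7 and 0.9, and by about 4% at ICC 0.10 with r = 0.8 and stable sub parish effects. The gain would be material for power only if r were near 0.5.

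These sizes rest on an assumed r, because the article gives none, and on equal variances over time. The gain also requires equal expected baseline means, so recruitment within sub parishes must not depend on arm. The article plans to blind group leaders and participants to arm but does not state whether recruitment precedes randomisation. This is a condition to confirm, not a fault found.

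Nothing here shows that the planned analysis is biased, or that the trial is underpowered because of it.

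**What to change.** Keep the three-occasion linear mixed model with sub parish and participant as random effects and age as a covariate. Constrain the baseline means to be equal across arms: no treatment term at M1, with arm-by-time terms at M2 and M3 only. Report the between-arm difference at M2 as the primary effect on waist. With equal baseline means this targets the same quantity as the difference in change.

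The coding needs care. The plan uses M2 as the reference occasion, and dropping the treatment main effect under that coding would force the arms to be equal at M2. M1 must be the reference.

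Do not offer individual-level analysis of covariance as an equivalent alternative. State that the constraint relies on recruitment being independent of arm, and keep the planned unconstrained contrast if that cannot be confirmed.

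The cost is one or two sentences in the analysis section, with no extra women, visits or measurements.

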### Step VI: Development of an evaluation plan

#### Study design, setting and timing

The effectiveness of the intervention will be evaluated through a cluster-randomized controlled trial. The intervention will be evaluated in Kampala, the capital city of Uganda. The six sub parishes of Mbuya catholic parish will be randomized to treatment and control arms, Fig. 4. The treatment arm will be exposed to both the developed intervention infographics and face to face group sessions while the control arm will only receive the developed intervention infographics. An awareness session will be organized to distribute the infographics to the control arm. Within the sub parishes, there are existing women groups. These existing groups will be utilized for face-to-face intervention group sessions. For the intervention purposes, each group will be limited to a maximum of 14 members. The study period is divided into two phases: a three-month intervention and a three-month post-intervention follow-up phase.

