#### Inclusion criteria

i)Sex (women),ii)Age (18 to 45 years),iii)Central obesity [waist circumference ≥ 80 cm]),iv)Fluent in either Luganda or English (sessions will be conducted in Luganda/English).v)Willingness to follow the three-months intervention and three months follow-up,vi)Willingness to sign the informed consent.

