Fourth, the intervention is designed with a combination of eleven evidence based BCT, scientifically proven to enact changes in knowledge, skills, self-efficacy, subjective norms, and social support to create a sustainable behaviour change [20, 35, 36, 43]. The limitation is that the evidence for the effectiveness of the BCT is exclusively from HIC due to lack of evidence in urban SSA. Questions may be raised on the applicability and effectiveness of scientifically proven BCT in HIC in urban SSA. Theoretically, scientifically proven BCT in the HIC, could positively influence behaviour change in other settings provided they are translated into practical strategies with critical consideration of parameters of use documented by Eldredge, Markham [20]. In our intervention, we carefully considered the parameters of use suggested by Eldredge, Markham [20]. If successful, the intervention could contribute evidence on the validity/applicability of scientifically proven BCT in High Income Countries in urban SSA and how they can be translated.

Fifth, our intervention equips participants with skills and self-efficacy to evaluate nutrition information. Studies show that over the last decade, the virtual environment has become an important determinant of dietary and PA behaviour [46]. A lot of nutrition information is shared on social and mass media, yet majority of the public lacks the skill and self-efficacy to distinguish between factual and non-factual nutrition information. Lastly, in our evaluation design of the intervention, we have included a post intervention follow-up measurement moment. This allows us to analyse the long-lasting effect of the intervention.

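### A participant random intercept alone gives every time-by-treatment contrast the same standard error, which is too large or too small if within-woman correlation differs between visit pairs

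*Protocol article*

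**What the plan says.** The Data analysis section of the protocol article sets out the hierarchy: "We will define two levels in our multi-level analysis: (1) participant and (2) sub parishes". The fixed effects are time, treatment and their interaction, "as well as age will be specified as fixed effects, and sub parishes and participants as random factors". No random slope, visit-specific variance or residual correlation structure is mentioned.

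Waist circumference is measured at months 0, 3 and 6 (M1, M2, M3): "The study period is divided into two phases: a three-month intervention and a three-month post-intervention follow-up phase". The named time comparisons start from M2, which "will be compared with base-line measurement (M_1_) and post-follow up measurement (M_3"). Other comparisons are left to Tukey or Benjamini–Hochberg procedures "when performing post hoc analyses to further identify differences within treatments as well as between time points".

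On model checking, "compatibility with mixed-model assumptions will be checked by inspection of residual plots and Q-Q plots", with log transformation as the stated response to heteroscedastic residuals. The Discussion says of the follow-up visit: "This allows us to analyse the long-lasting effect of the intervention".

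**The concern.** A random intercept per woman plus independent residuals of equal variance is compound symmetry: the same variance at each visit and the same correlation for each pair of visits. Under that model the changes over 0–3, 3–6 and 0–6 months all have the same variance, estimated by pooling the three. Repeated body measurements often correlate less as the interval between them grows. If that happens here, the pooled figure is too large for 3-month changes and too small for the 6-month change.

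At stake are power for the two named contrasts, and false-positive control for month 6 against baseline, the comparison that most directly answers the question of a lasting effect. The same kind of model is planned for each outcome, so the assumption carries over to the secondary outcomes.

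**Working it through.** **The plan's own figure.** (1.96 + 0.842)² × 2 × 13.73² / 7.4² = 54.06. Multiplied by the design effect 1 + 26 × 0.001 = 1.026, this gives 55.46, against the stated 55 per arm (66 after the 20% increase). It uses one cross-sectional SD and no correlation between visits, so the covariance model does not alter it.

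**Inputs.** Two-sided 5% level (1.96) and 80% power (0.842) come from the sample size section. No within-woman correlation or SD by visit is given anywhere, so every such value below is an assumption. Data are taken as complete and balanced, with no sub-parish variation in change.

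**Formula.** Let V12, V23 and V13 be the true variances of a woman's change between the visit pairs. The random-intercept model uses (V12 + V23 + V13)/3 for every contrast. Set V12 = V23 = 1 and V13 = c. The ratio r of model SE to true SE is:

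- either 3-month contrast: r = √((2 + c)/3)
- month 6 against baseline: r = √((2 + c)/(3c))

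Type I error is 2(1 − Φ(1.96r)). A contrast with 80% power under the correct SE has power Φ(2.802 − 1.96r).

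| c | r, 3-month contrasts | Type I error | Power (from 80%) | r, month 6 v. baseline | Type I error |
|---|---|---|---|---|---|
| 1 | 1.00 | 5.0% | 80% | 1.00 | 5.0% |
| 1.25 | 1.04 | 4.1% | 78% | 0.93 | 6.8% |
| 1.5 | 1.08 | 3.4% | 75% | 0.88 | 8.4% |
| 2 | 1.15 | 2.4% | 70% | 0.82 | 11.0% |

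For example, at c = 2, r = √(4/3) = 1.155 and 1.96r = 2.263, giving 2.4%. For month 6, r = √(4/6) = 0.816 and 1.96r = 1.600, giving 11.0%.

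**In terms of correlations (equal SDs).**

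- Equal correlation of 0.9: all ratios are 1.00.
- Mild decay, 0.90/0.90/0.87 for pairs 1–2, 2–3 and 1–3: c = 0.13/0.10 = 1.3. Ratios are 1.05 for both 3-month contrasts (4.0%) and 0.92 for month 6 against baseline (7.1%).
- First-order autoregressive with correlation 0.70 to 0.95: c = 1.70 to 1.95. Ratios are 1.11 to 1.15 (3.0% to 2.5%) and 0.85 to 0.82 (9.5% to 10.7%).
- Change more variable in the intervention phase, 0.85/0.95/0.85: change variances are proportional to 0.30, 0.10 and 0.30, with mean 0.233. Ratios are √(0.233/0.30) = 0.88 for M2–M1 and M3–M1 (8.4% each), and √(0.233/0.10) = 1.53 for M3–M2 (0.3%).

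**Simulation.** 55 women per arm, 4,000 runs per pattern, type I error for M2–M1, M3–M2 and M3–M1:

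- equal correlation 0.9: 5.7%, 5.2%, 5.4%
- autoregressive 0.9: 2.7%, 2.7%, 10.6%
- mild decay: 3.9%, 3.9%, 7.5%
- 0.85/0.95/0.85: 9.1%, 0.2%, 8.7%

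A random-intercept model fitted to one simulated data set gave the same SE, 1.254, for both interaction terms, as the formula implies.

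**Entry floor.** Eligibility requires "waist circumference ≥ 80 cm", which truncates baseline only. Assume a population mean of 82 cm, SD 13.73 and the same correlation of 0.90 (or 0.95) for every visit pair. Baseline variance is then 0.396σ², and month-3 variance is 0.511σ² (0.455σ²), which is 29% (15%) higher. The change variances hardly move. At 0.90 they are 0.194σ² for both changes from baseline and 0.200σ² for M3–M2, so the model SE is 0.5% too large and 1.0% too small respectively. At 0.95 the figures are 0.3% and 0.5%.

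**The case against.** The article does not use the term random intercept, does not rule out slopes, and condenses a fuller protocol; a covariance structure and convergence rules are often left to an analysis plan. A random intercept is also a common choice with three visits, and nothing in the section contradicts another. What stands is that the reading is an inference. It is nevertheless the plain one: the levels are listed, the random factors are named, no slope appears, and a random effect of categorical time per woman plus a residual is not identifiable with one analysed value per visit. The point therefore concerns a stated choice, not a missing detail.

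A reader might infer that the standard errors are definitely wrong, and wrong in both directions for the planned comparisons. The documents do not support that. They give no correlations, and equal correlation leaves no error. Both named contrasts span three months, so simple decay makes both conservative. The inflated contrast, month 6 against baseline, is only a possible post hoc comparison, and the Discussion's remark about lasting effect names no contrast.

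A reader might also take the 80 cm floor as evidence. It does breach equal variance, but it shifts contrast SEs by 1% or less and should not be used as support.

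The planned safeguards do not close the gap. Residual and Q-Q plots are not designed to show correlation falling with lag, log transformation does not repair it, and a multiplicity procedure adjusts p-values that already rest on the pooled SE.

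**Conclusion.** The concern holds in conditional form. As written, the model implies compound symmetry and offers no alternative. For an assumed change-variance ratio of 1 to 2, the SEs of the two named contrasts are correct to about 15% too large, and the SE of month 6 against baseline is correct to about 18% too small (type I error 5% to about 11%). The direction is not fixed: if change is more variable during the intervention phase, month 3 against baseline can itself be anti-conservative, at about 8% with correlations 0.85/0.95/0.85. The power loss from 80% to about 70% describes a contrast that would have 80% power with the correct SE; it is not an estimate of this trial's power. The issue lies within women and arises even if sub parishes do not differ. It is worth correcting because the remedy is cheap.

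**What to change.** In the Data analysis section, replace the participant random intercept with an unstructured within-woman covariance over M1, M2 and M3: a variance for each visit and three correlations. Keep the sub-parish terms. In R this is a visit-specific variance with a general correlation matrix. Name in advance one simpler heterogeneous structure to use if the model does not converge, preferably one that lets correlation fall with lag, such as visit-specific variances with a first-order autoregressive correlation.

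The cost is about one sentence and no new data. Covariance parameters within women rise from two to six, so four more are estimated from 110 to 132 women, and convergence may fail for some outcomes, hence the fallback. Compound symmetry is a special case of the unstructured form, so little is lost if the simpler assumption is true.

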### Recruitment

The PhD researcher and women leaders of existing groups will make presentations about the intervention during one of the routine meetings. Flyers with details of the intervention will be distributed for sharing with members who are absent during the briefing. At the end of the presentations, interested participants will be invited for the first session to test their eligibility to participate in the study. Eligible participants will be provided with an informed consent form to endorse.

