### Outcomes

Primary outcome is reduction in waist circumference. Decreases in waist circumference are recommended as critically important treatment target for reducing adverse cardiometabolic health risks [15]. Secondary outcomes include optimisation of, fasting blood glucose, total cholesterol, HDL, LDL, triglycerides, body composition, food literacy, PA, and fruit and vegetable intake.

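### Post hoc significance tests of change within each arm are not randomised comparisons and, because entry requires a waist of at least 80 cm, lean towards a fall; the plan should rest effectiveness on the between-arm contrast alone

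*Protocol article*

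**What the plan says.** The Outcomes section of the protocol article states: "Primary outcome is reduction in waist circumference". The inclusion criteria select on the same variable: "Central obesity [waist circumference ≥ 80 cm". Under Recruitment, "interested participants will be invited for the first session to test their eligibility to participate in the study". The article does not say whether that eligibility reading also serves as the baseline value.

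The Data analysis section sets up a linear mixed model. Its purpose is comparative: "To assess changes in metabolic health between the intervention and control groups". In it, "treatment (and interaction of time and treatment) as well as age will be specified as fixed effects", with sub parish and participant as random factors. Time is coded with the end-of-intervention measurement (M2) compared with baseline (M1) and with the post-follow-up measurement (M3).

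The section then adds a further layer: "Tukey or Benjamini–Hochberg procedures will be applied when performing post hoc analyses", the purpose being "to further identify differences within treatments as well as between time points". One threshold covers everything: "p < 0.05 will be considered significant in all analyses".

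Three things are not stated: that the post hoc tests depend on a significant interaction, that they are descriptive, and that effectiveness is judged only between arms. No between-arm contrast at M2 or M3 is named among the post hoc analyses.

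**The concern.** A test of change within one arm compares women with themselves at an earlier date. It takes in everything that moves waist over three or six months, and here there are at least two such influences besides the group sessions. First, selecting women because their waist is at or above a cut-off makes the mean drift down on re-measurement even if nothing happens (regression to the mean). Second, the control arm also receives the infographics, and both arms are measured repeatedly.

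A multiplicity adjustment controls the number of chance findings. It does not remove a bias that every within-arm test of waist shares. A significant fall in the treatment arm beside a non-significant fall in the control arm is not a test of the difference between arms either. With a single 0.05 rule for all analyses, a trial with no intervention effect could still yield a within-arm reduction in the primary outcome that is labelled significant.

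Naming two multiplicity procedures without a rule for choosing adds a smaller uncertainty. Tukey controls the family-wise error and Benjamini–Hochberg the false discovery rate, and the two can disagree on the same p-value.

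**Working it through.** **Inputs from the protocol article.** Waist SD 13.73 cm, effect 7.4 cm, cluster size 27 and ICC 0.001 (Table 3); entry cut-off 80 cm (Inclusion criteria); 66 women per arm (Sample size calculation).

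**Inputs assumed, because the article does not give them.** Mean waist in the source population, 75 to 95 cm. Correlation r between the selecting reading and the three-month reading, 0.90 to 0.99. Normal distribution. Selecting reading used as baseline.

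**1. The plan's own figure.** (1.96 + 0.842)² × 2 × 13.73² / 7.4² = 54.06. Multiplied by the design effect 1 + 26 × 0.001 = 1.026, this is 55.46, which the article writes as 55. Then 55 × 1.2 = 66 per arm. The figure reproduces, and 66 is used below.

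**2. Expected fall with no true change.** Let a = (80 − mean)/13.73 and λ = φ(a)/(1 − Φ(a)). The expected fall is 13.73 × (1 − r) × λ.

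- Mean 75: a = 0.364, λ = 0.3733/0.3579 = 1.043. At r = 0.90 the fall is 13.73 × 0.10 × 1.043 = 1.43 cm.
- Mean 80: a = 0, λ = 0.3989/0.5 = 0.798. At r = 0.95 it is 13.73 × 0.05 × 0.798 = 0.55 cm.
- Mean 85: a = −0.364, λ = 0.3733/0.6421 = 0.581. At r = 0.95 it is 13.73 × 0.05 × 0.581 = 0.40 cm.
- Mean 95: a = −1.093, λ = 0.2197/0.8627 = 0.255. At r = 0.99 it is 13.73 × 0.01 × 0.255 = 0.03 cm (0.035 before rounding down).

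**3. How often a within-arm test calls this significant.** Null trials were simulated (4,000 per scenario, 66 per arm, no intervention effect, no time trend, no cluster effect). Each arm had a paired t test, unadjusted and with the Tukey critical value for three time points. The arms were also compared on change.

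| Source mean, r | Fall (cm) | Significant fall in a given arm, unadjusted | Same, Tukey | Between-arm test |
|---|---|---|---|---|
| 75, 0.90 | 1.43 | 47.8% | 33.8% | 4.8% |
| 80, 0.95 | 0.55 | 18.6% | 10.7% | 5.0% |
| 85, 0.95 | 0.40 | 11.4% | 6.3% | 4.6% |
| 95, 0.90 | 0.35 | 6.0% | 2.8% | 4.3% |
| 95, 0.99 | 0.03 | 3.5% | 1.7% | 5.2% |

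The nominal rate for a fall is 2.5% for one unadjusted test. The Tukey limit for one contrast corresponds to about half of 0.019, or roughly 1%. Over all scenarios, including runs with 55 per arm, the between-arm rate lay between 4.3% and 5.9%. Both arms carry the same bias, so it cancels in the difference.

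**4. Reading one arm against the other.** Suppose both arms fall by 1 cm, with an SD of change of 4 cm and 55 women per arm (assumed values). Each within-arm test is significant with probability 0.444, so exactly one arm is significant in 2 × 0.444 × 0.556 = 49% of trials unadjusted. With Tukey this is about 43% over three time points and 28% over six arm-by-time means. The true difference between arms is zero throughout.

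**5. Tukey against Benjamini–Hochberg.** Over three time points Tukey needs a raw p below about 0.019. Benjamini–Hochberg needs 0.05/3 = 0.0167 if only the smallest p-value is to be accepted, 2 × 0.05/3 = 0.033 for the second smallest, and 0.05 if all three lie at or below it. A lone p of 0.018 passes Tukey and fails Benjamini–Hochberg. A second-ranked p of 0.03 does the reverse. Over six means (15 pairs) the limits are 0.0044 for Tukey and 0.05/15 = 0.0033 for a lone p-value under Benjamini–Hochberg. Neither is stricter in every case.

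**The case against.** The strongest reply is that the randomised comparison is already in the plan. The model is introduced as a comparison of change between the two groups, and its interaction of time and treatment gives the between-arm difference in change from M1 to M2. M3 against M1 follows from the same model as a linear contrast. The post hoc tests come afterwards as a supplement, and looking at simple effects after an interaction is ordinary practice. All of this stands.

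A reader might infer that the trial will claim effectiveness from within-arm falls, or that the primary analysis is biased. The document supports neither. No sentence says efficacy is judged within arms, and the selection bias cancels in the interaction. A reader might also infer that the multiplicity procedure will be picked after the results are seen. The article does not say when the choice is made. The two names may belong to different families of tests, and an analysis plan that is not shown may settle it.

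The size is open to dispute as well. The source mean and the correlation are assumptions. At a mean of 95 cm the Tukey-adjusted rate is about 2% to 3%. Table 4 has waist taken twice, which reduces technical error, and a separate baseline reading after the eligibility check would shrink the bias. The mechanism acts directly on waist and only weakly on outcomes not used for selection. The 49% in the working is not a false-positive rate, because a common fall could be a real change: both arms receive the infographics.

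What the reply does not remove is that the article commits to within-arm significance tests on a variable used for selection, under a common 0.05 rule, and does not confine conclusions about effectiveness to the between-arm contrast.

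**Conclusion.** The point holds as a weakness in the follow-up tests and their interpretation. As far as this selection bias goes, the planned interaction is a valid between-arm comparison and the primary model is not affected. The added within-arm tests are not randomised comparisons, and for waist they lean towards a fall in both arms.

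With no true change the fall is about 0.03 to 1.4 cm. With 66 women per arm, the chance of a spurious significant fall in a given arm is about 3.5% to 48% unadjusted and 1.7% to 34% with Tukey. These ranges rest on an assumed source mean of 75 to 95 cm, a correlation of 0.90 to 0.99, normality, and use of the selecting reading as baseline. The direction of the bias is firm under these assumptions; its size is uncertain and may be negligible. The between-arm figure near 5% speaks only to this bias, since the simulation had no cluster effect.

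The open choice between two multiplicity procedures is a lesser matter, but it can change the verdict on a borderline p-value in either direction. The change is worth making because it costs only wording.

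**What to change.** In the Data analysis section:

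- State that effectiveness is judged on the between-arm difference in change from baseline at M2 and at M3, both taken from the planned interaction model, each with a 95% confidence interval. Name the M3-versus-M1 contrast explicitly, because the present wording takes M2 as the point of comparison.
- Report within-arm changes descriptively (means and changes by arm and time), without significance claims.
- Name in advance one multiplicity procedure for the two between-arm contrasts, for example Holm, in place of the choice between Tukey and Benjamini–Hochberg.

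The cost is analysis wording only, with no change to recruitment, measurement or sample size. The small downside is that there will be no p-value for change within an arm.
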